## Materials and methods

### Study design

A clinical longitudinal experimental design with inter-subject comparisons was employed, with the aim of comparing an experimental group (i.e., individuals receiving psychological treatment) and a control group on the waiting list (i.e., those without treatment) at three time points: before treatment (T1), and two post-treatment time points (T2, T3). The control group hasn’t any alternative activities or exposure to placebo-like interactions. Furthermore, an intra-subject analysis was conducted by comparing repeated measures to observe changes within the same individuals before (with pre-treatment measurements, T1), after 6 weeks (T2, in the control group and post-treatment in the experimental group), 6 months after T2 (T3, in the control group and post-treatment in the experimental group).

Initially, immediately after completing the informed consent online, a first evaluation will be conducted for all participants (T1), covering the main areas that constitute the psycho-emotional state of the participants. Following this first evaluation, participants in the experimental group will engage in six weeks of gameplay, with each week dedicated to completing one mission of *emoTICare*. At the six-week mark after the initial evaluation, and immediately following the completion of the *emoTICare* application by participants in the experimental group, a second evaluation (T2) of all participating adolescents (control and experimental groups) will take place. Following a period of six months from T2, a subsequent measurement, designated T3, will be conducted in all participants.

T1 will serve as the baseline measure of the psycho-emotional state of participating adolescents before the commencement of the *emoTICare* intervention. The homogeneity of the control group will be evaluated by comparing the T1 scores of both the control and experimental groups to ensure no significant differences exist, thereby allowing for comparable study groups. T2 will also function as a control measure for all participants concerning the evaluated variables. However, in the control group, only the changes resulting from the natural progression of time without intervention will be examined, while in the experimental group, the benefits achieved in these variables following the *emoTICare* intervention will be analyzed. T3, the follow-up measure, will also function as a control measure after six months for all participants with regard to the evaluated variables.

This experimental study includes a randomized clinical trial aimed at assessing the effects of completing the *emoTICare* program concerning the socio-emotional competencies and psychological well-being of these adolescents. The method employed for generating allocation sequences was a computerized random number generator. The sequence generation was based on a process of simple randomization, founded upon a single sequence of random allocations. The R programme was employed to allocate the participants at random to distinct groups (control and experimental) with equal probability. Consequently, it was guaranteed that every participant had an equal probability of being placed in any group. In order to guarantee allocation concealment and minimise selection bias, the allocation process was conducted in a controlled and secure environment. The sequence generated by the R program was stored in such a way that the researchers responsible for allocation did not have access to allocation information prior to the inclusion of participants in the study. Furthermore, the allocation was executed by an independent researcher external to the team, who interacted directly with the participants, thereby facilitating the maintenance of blinding. The integrity of the procedure was ensured through regular monitoring, and any possibility of manipulation of the allocations was avoided. This ensured that both the participants and the researchers responsible for the intervention were blinded to the assigned group, thus minimising any possible selection bias and ensuring the validity of the results.

The principal investigator will be responsible for obtaining informed consent from the participants (adolescents and parents/legal guardians) by informing them about the study. Adolescents aged between 12 and 16 inclusive will be required to sign the consent form in conjunction with their guardian, while those aged 16 and over will be permitted to sign it directly.

The collection of data will be facilitated through the utilisation of the Limesurvey platform, wherein the participants will be prompted to complete questionnaires in an anonymous manner. The principal investigator will supervise access and data security, and the research team will only access anonymised data for analysis.

The research team will measure baseline data at the commencement of the study through online questionnaires, and also the two post-test measures. The randomisation process will be overseen by the principal investigator and team, and will be conducted using a computerised random number generator.

The research team will be responsible for configuring and training participants and staff on the use of the Limesurvey platform, ensuring proper usage of the system.

According to the Standard Protocol: Recommendations for Interventional Trials statement [49], the current study protocol outlines the details of the study rationale, objectives, interventions, methods and statistical analyses, organization, and ethical considerations (See Figs 1 and 2).

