### Objectives

The main objectives of this study are: (1) to design and implement a *serious game* called *emoTICare* to promote physical and emotional health, as well as the development of socio-emotional skills among adolescents with Type 1 Diabetes Mellitus (T1DM) through a psychological intervention conducted on a technological platform that incorporates artificial intelligence and Ecological Momentary Assessment (EMA); (2) to analyze the effectiveness of this *serious game* on indicators of disease adjustment, quality of life, and socio-emotional well-being, as well as improvements in socioemotional competencies and skills.

The study hypothesizes that adolescents will maintain or improve their physical and emotional health indicators following the *emoTICare* program. Specifically, statistically significant improvements (*p* ≤ .05) are expected in the following variables: health-related quality of life, social skills and communication, emotional awareness, resilience, self-esteem, as well as coping and problem-solving abilities. Additionally, a statistically significant reduction (*p* ≤ .05) is anticipated in variables related to the perceived threat of the disease, as well as emotional and behavioral problems. The experimental group is expected to show improvements in all these areas when comparing pre- and post-treatment evaluations, and also in comparison to the control group on the waiting list.

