The primary focus of this study is on the evaluation of the programme’s overall effectiveness, as opposed to the presentation of definitive assertions concerning the outcomes of individual participants. It is imperative to emphasise that the tests are embedded in pre-specified models, with the primary focus being on assessing the overall effectiveness of the programme.

Before testing the change models, descriptive analyses, Pearson correlations, and multivariate and univariate analysis of variance (MANOVA and ANOVA) will be conducted using pre-intervention scores for participants in experimental and control groups to identify potential baseline differences. Furthermore, multivariate and univariate analysis of covariance (MANCOVA and ANCOVA) will be performed to detect changes in post-intervention scores (short-term effect), with pre-intervention scores as a covariate. These analyses will focus on latent variables derived from the composite scores of multiple Likert items, which represent underlying constructs such as emotional symptoms or health-related quality of life. Effect sizes (Cohen’s *d*) for each variable will also be calculated to estimate the magnitude of differences between the experimental and control groups. These analyses will be conducted using SPSS V.28.

To ensure the reliability of the results, we will begin with a series of diagnostic tests and validation procedures. This will include an analysis of residuals to assess the goodness of fit of the model, using residual plots and tests for normality (e.g., Q-Q plots and Shapiro-Wilk test). Homoscedasticity will be evaluated through the Breusch-Pagan or White’s test, and the Durbin-Watson statistic will be used to check for autocorrelation in the residuals. These tests will allow us to ensure that the assumptions of the parametric models are met. Additionally, we will conduct cross-validation (k-fold) to ensure that the model generalizes well to unseen data and is not overfitted. We will also perform outlier detection using Cook’s distance and leverage plots to examine the influence of individual data points on the model.

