Multiple hierarchical regression analyses will be conducted to examine the added predictive value of the experimental condition in explaining the intervention program’s efficacy. Hierarchical regression is a stepwise method where predictors are added to the model in blocks. The rationale behind the hierarchical approach is to assess the incremental contribution of each new block of predictors while controlling for the variables entered in the previous blocks. This allows for a clearer understanding of the unique variance explained by the experimental condition, after accounting for initial factors.

Step 1: The first block typically includes variables measured at time 1 that are believed to influence the dependent variable (i.e., the change between T2-T1 and T3-T1 for each variable). These could include baseline measures of emotional symptoms, quality of life, or disease-related factors.

Step 2: In subsequent blocks, new independent variables (predictors) are added. For example, in the second block, we would add the experimental condition (treatment vs. control) to assess its impact on the change in the dependent variable, controlling for the baseline scores. The dependent variable will be the change between pre- and post-intervention scores, as well as between pre-intervention and follow-up scores. A statistically significant change in the coefficient of determination in Model 2 (predictor: experimental condition, controlling for pre-intervention score) will be interpreted as added predictive value. A significant prediction from the experimental condition, controlling for pre-intervention score, will allow attribution of significant change to the intervention.

The Reliable Change Index (RCI) will be calculated for the scores of the evaluated variables. Reliable change will be determined by the extent to which an individual’s progress exceeds the natural fluctuation of measurements [80]. The RCI will be calculated using pre- and post-*emoTICare* means, along with the pre-intervention standard deviation and Cronbach’s alpha index.

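### Game-arm change is labelled benefit while the same change in controls is labelled natural progression, which conflicts with the plan's own between-arm attribution rule

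*Protocol article*

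**What the plan says.** Three parts of the protocol article bear on how change within the game arm is to be read.

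- **Study design.** For T2, "in the control group, only the changes resulting from the natural progression of time without intervention will be examined". The game arm gets a different label in the second half of that sentence, which speaks of benefit: "in the experimental group, the benefits achieved in these variables following the" (the sentence then names the intervention). The same section states that "an intra-subject analysis was conducted by comparing repeated measures to observe changes within the same individuals", across T1, T2 and T3 and in both groups. It names no test and no decision rule for this.
- **Objectives**, with nearly the same wording in the Abstract. After listing the variables expected to change at p ≤ .05, the text says: "The experimental group is expected to show improvements in all these areas when comparing pre- and post-treatment evaluations". The contrast with controls is then added as a second expectation: "and also in comparison to the control group on the waiting list".
- **Data analysis.** MANCOVA and ANCOVA on post-intervention scores are planned "with pre-intervention scores as a covariate". A hierarchical regression on T2−T1 and T3−T1 change enters baseline first and arm second. It lets change be attributed to the intervention when arm is a significant predictor with the pre-intervention score controlled. The section also plans a Reliable Change Index: "The RCI will be calculated using pre- and post" emoTICare means, the pre-intervention SD and Cronbach's alpha. No control-arm term is stated.

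**The concern.** The Study design sentence recognises natural change but allows for it in one arm only. Under randomisation, the natural course and the effect of answering the same questionnaires again are the same in expectation in both arms. Game-arm change is therefore natural course plus retest effect plus any effect of the game. Only the difference between arms isolates the last term, and supplying that difference is the purpose of the waiting list.

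The protocol thus holds two readings of the same number. In Study design, game-arm change is benefit as it stands. In Data analysis, change is credited to the intervention only through the arm effect. The Abstract and Objectives list the within-arm improvement as an expected result, and no text ranks it below the between-arm contrast. If the game arm improved and the arms did not differ, the Study design wording would still leave room to describe that improvement as benefit, which the Data analysis rule would not support.

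**Working it through.** **Inputs from the protocol article.** Total sample 372 and 20% dropout (Sample size); 1:1 simple randomisation (Study design); analysis restricted to those who complete all three measurements (Measurements); significance level .05 (Abstract, Objectives). Completers per arm: 372 × 0.8 / 2 = 148.8, taken as 149. The figure 372 is used as stated; how it was derived does not affect this point.

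**Assumptions, not in the article.** Two-sided testing; no game effect; a favourable drift g, in baseline SD units, common to both arms; T1–T2 correlation r; equal SDs at T1 and T2.

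**Within-arm test.** The SD of individual change is √(2(1−r)). The paired t statistic has 148 degrees of freedom and noncentrality g√n / √(2(1−r)).

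- g = 0.10, r = 0.5: SD of change 1.000, noncentrality 0.10 × 12.21 / 1.000 = 1.22, probability of significant improvement 22.7%.
- g = 0.20, r = 0.8: SD of change 0.632, noncentrality 0.20 × 12.21 / 0.632 = 3.86, probability 97.0%.

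Probability of a significant improvement in the game arm, per variable, with no game effect:

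| Common drift (SD) | r = 0.5 | r = 0.6 | r = 0.7 | r = 0.8 |
|---|---|---|---|---|
| 0 | 2.5% | 2.5% | 2.5% | 2.5% |
| 0.10 | 22.7% | 27.3% | 34.7% | 48.3% |
| 0.15 | 44.4% | 52.9% | 65.1% | 82.0% |
| 0.20 | 67.9% | 77.4% | 87.9% | 97.0% |

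The zero-drift row counts only the favourable tail. It corresponds to 5% two-sided, so the test then holds its level. With no dropout (186 per arm), the ranges over r are 27–57% at 0.10 SD and 77–99% at 0.20 SD.

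**Between-arm test on the same data.** A drift common to both arms cancels in the arm contrast. In 4,000 simulated trials at each drift (149 per arm, r = 0.6), the baseline-adjusted ANCOVA rejected in 5.2%, 4.5%, 5.2% and 5.2% of trials at drifts of 0, 0.10, 0.20 and 0.30 SD. The simulation takes completers in the two arms to be comparable; whether the per-protocol restriction preserves that is a separate question.

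**The case against.** The strongest reply is that the formal rule is already correct. Data analysis ties attribution to the arm effect with the pre-intervention score controlled, for both T2−T1 and T3−T1 change, and the ANCOVA is a between-arm model. The Objectives join the two expectations with "and also in comparison to the control group on the waiting list". If both are required, common drift cannot satisfy the pair, and the false-positive rate is capped by the between-arm test at about 5%. All of this stands, and it limits the point.

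A reader might infer more: that the trial will declare success on the within-arm test alone, or will set a significant change in one arm against a non-significant change in the other. The article supports neither. It speaks of expected results and never makes within-arm significance sufficient. It does not propose comparing within-arm p-values across arms. The intra-subject analysis covers both groups and is there to observe change. The Data analysis section lists no standalone paired test, so the 23–97% describes a criterion the protocol does not adopt by itself.

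Nor is favourable drift established. The pre-to-post contrast spans six weeks, and the Introduction links chronic illness in adolescence with difficulty and declining quality of life. If drift were unfavourable, a within-arm reading would err the other way and could hide a real effect.

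What the reply does not remove is the conflict between Study design and Data analysis, or the absence of any statement that the within-arm result is subordinate.

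**Conclusion.** The point holds as a matter of wording and hierarchy. The planned models are sound on this issue. The Study design sentence is not: it credits to the game a change that the next section will credit only after comparison with controls, and nothing settles which reading prevails when they disagree.

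The 23–97% range shows how far the two readings could diverge. It rests on a drift of 0.10–0.20 SD and a correlation of 0.5–0.8, neither of which the article gives, and it is not a predicted error rate for this trial. The qualitative conclusion needs neither value: any common drift moves the within-arm comparison and leaves the between-arm one alone.

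**What to change.** 1. In the Abstract and Objectives, state that effectiveness is judged only by the between-arm difference, adjusted for T1, at T2 and at T3, using the models already in Data analysis.
2. In Study design, replace the asymmetric sentence with one saying that natural change is estimated in the controls and that the effect of emoTICare is the difference between the arms.
3. Report within-arm changes, and the Reliable Change Index, for both arms as description, without attributing them to the game. Whether p-values accompany them is a reporting choice.

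The cost is a few sentences. No new data, participants or models are needed. The Eligibility and recruitment criteria section says that recruitment, data collection and final results are all still incomplete, so the change can precede the final analysis. What is given up is the option of presenting a favourable within-arm change as evidence of effect when the arms do not differ.

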The phase encompassing the evaluation of the variables of interest, T1-T2-T3, will take place through the survey platform of the Universitat de València, Limesurvey, from September 2024 to the end of February of 2027. The response platform for the questionnaire battery includes a consent form for anonymous participation in the study. In this platform, informed consent will be obtained from the parents or legal guardians of the participants, as well as from the minors themselves, ensuring that all are informed about the anonymity and confidentiality of their data, confirming that their participation in the study is voluntary.

To access and play the *emoTICare serious game* online for six weeks (one week per mission of the game), participants will be provided with a link at the end of the evaluation survey conducted at T1. This *serious game* contains six distinct areas, each designed to be completed within a maximum of one week, thus allowing sufficient time to progress at different paces. During the period in which the adolescents are completing the *serious game*, an email address and a mobile phone number will be made available for participants to contact in case they need assistance (see Table 1).

**Table 1 pone.0325763.t001:** Intervention timeline.

				Timeline (in months)																															
	2024							2025												2026												2027			
	Jun	Jul	Aug	Sep	Oct	Nov	Dec	Jan	Feb	Mar	Apr	May	Jun	Jul	Aug	Sep	Oct	Nov	Dec	Jan	Feb	Mar	Apr	May	Jun	Jul	Aug	Sep	Oct	Nov	Dec	Jan	Feb	Mar	Apr

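### The protocol says participants were blinded to their group, but a game compared with an empty waiting list cannot be blinded to those who play or wait, and the six primary outcomes are questionnaires they complete themselves

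*Protocol article*

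**What the plan says.** The Study design section describes a computer-generated simple randomisation sequence. It was stored out of reach of those allocating until participants were included. On who carried out the allocation it says: "the allocation was executed by an independent researcher external to the team, who interacted directly with the participants". It then states: "This ensured that both the participants and the researchers responsible for the intervention were blinded to the assigned group", and closes with "thus minimising any possible selection bias and ensuring the validity of the results".

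The same section describes the comparator as "a control group on the waiting list (i.e., those without treatment" and adds: "The control group hasn’t any alternative activities or exposure to placebo-like interactions". The experimental group plays for six weeks, one mission a week. On access to the game, the text before Table 1 says that "participants will be provided with a link at the end of the evaluation survey conducted at T1", and that an email address and a mobile number are available for help during play.

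The Measurements section lists six primary outcomes: KIDSCREEN-27, SDQ, EAQ-30, CAG, SPSI-R and CHASO. All are questionnaires that participants complete online. The limitations in the Discussion mention socially desirable answers and misread questions, but not that respondents know their group.

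**The concern.** Allocation concealment and blinding protect against different things. Concealment keeps the next assignment unknown until a participant is in the trial, which limits selection bias. Blinding keeps the assignment unknown afterwards, which limits bias in behaviour and reporting. The protocol lists concealment measures and then claims blinding as their result.

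This matters because the outcomes depend on the respondent's judgement. An adolescent who has played a game meant to improve well-being, or who has been left waiting, may answer differently for that reason alone. The Data analysis section says that a significant effect of condition, controlling for the pre-intervention score, allows the change to be attributed to the intervention. A reader who believes participants were blinded has no reason to consider reporting bias as a rival explanation. A risk-of-bias assessor would credit a safeguard that the trial does not have.

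**Working it through.** **Comparison of the text (the finding rests on this alone)**

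| Question | Protocol article | Consequence |
|---|---|---|
| What do controls receive? | Waiting list, nothing placebo-like (Study design) | No sham that could mask the arm |
| What does the experimental arm receive? | A six-week game, reached by a link after T1 (Study design) | The participant sees whether a game arrived |
| When are outcomes measured? | T2 after six weeks, T3 six months later, in all participants | Both follow-up measures are taken after the arm is known |
| Who completes the primary outcomes? | The participant, online | The unblinded person is the assessor |
| What do the safeguards do? | Sequence stored away from allocators before inclusion; external allocator | Concealment only |

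The sentence about the link does not restrict it to one arm, but the section says that only the experimental group plays. The claim of participant blinding therefore contradicts the design set out in the same section.

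For the researchers responsible for the intervention, the conclusion is an inference. The article does not say who issues access or staffs the help contacts. Whoever does so deals with people who are playing, and so would very likely know their arm.

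**Illustration of the stakes**

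The plan gives no figure for reporting bias, so there is none to reproduce.

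Inputs from the protocol article:
- 372 participants and 20% dropout (Sample size): 372 × 0.8 = 297.6, or about 149 per arm.
- Significance at 0.05, taken here as two-sided.

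Assumptions, none of them in the documents:
- equal arms with equal dropout
- no true effect
- reporting bias b of 0.1 or 0.2 SD
- correlation r between baseline and follow-up of 0 (unadjusted) or 0.6

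Formulas, in SD units:
- SE = √(1 − r²) × √(2/n)
- False-positive rate = P(Z > 1.96 − b/SE) + P(Z < −1.96 − b/SE)

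Unadjusted: SE = √(2/149) = 0.116.
- b = 0.1: b/SE = 0.86, rate about 14%.
- b = 0.2: b/SE = 1.73, rate about 41%.

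ANCOVA with r = 0.6: √(1 − 0.36) = 0.8, so SE = 0.8 × 0.116 = 0.0927.
- b = 0.1: b/SE = 1.08, rate about 19%.
- b = 0.2: b/SE = 2.16, rate about 58%.

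With b = 0 the rate is 5% in both cases. With all 186 per arm (372/2) analysed, the unadjusted rates are about 16% and 49%. Baseline adjustment does not remove a bias that arises after baseline. It shrinks the standard error, so the same bias is more often declared significant. All rates are per outcome.

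**The case against.** The kindest reading is that the authors meant allocation concealment: the listed measures are concealment measures, and the same sentence mentions selection bias. That probably explains how the sentence arose, but it does not rescue it. Concealment is named separately, and the text then says that people were blinded to the assigned group.

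It is also fair that the waiting list is openly described, that self-report bias is acknowledged in general terms, and that correcting the sentence changes no data or test. This makes the point one of reporting and interpretation, not a fault in choosing a waiting list.

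Several stronger readings are tempting, and the documents do not support them:

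- **That staff blinding is impossible.** The game is self-played software, and the team is said to analyse only anonymised data. An analyst could be blinded, and the roles of those who give access or support are not stated.
- **That blinding is invoked to defend the self-reported scores or the attribution to treatment.** The blinding sentence does not mention self-report. The attribution statement rests on the regression of change on condition and does not cite blinding. The link is a consequence for the reader, not an argument the authors make.
- **That the account of allocation contradicts itself.** The article also says: "The randomisation process will be overseen by the principal investigator and team". Oversight by the team and execution by an outsider can coexist, and consent obtained by the principal investigator is not in itself a breach. What is unclear is who can see the sequence.
- **That the results are known to be biased, or by how much.** Bias towards the hypothesis is plausible, but neither its direction nor its size is documented. HbA1c, listed under other outcomes, is not a questionnaire score, although it too is collected through an ad-hoc record.

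**Conclusion.** The claim of participant blinding is wrong as written. This follows from the comparator described in the same section and needs no assumption. Unblinding of those who deliver or support the game is very likely, but inferred. The described safeguards justify a statement about concealment and nothing further, so the closing assurance about valid results does not follow from them.

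The consequence is that an effect on any of the six primary questionnaires may partly reflect knowledge of the arm. If that bias were 0.1 SD, a true null would be declared significant about 14% to 19% of the time per outcome instead of 5%. At 0.2 SD the range is about 41% to 58%. These figures depend on the assumed bias, on r between 0 and 0.6, and on 149 analysed per arm. They show sensitivity and are not estimates for this trial. Correcting the text would not lower them, but it would let readers allow for them.

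**What to change.** 1. Replace the blinding sentence in Study design with a statement that participants, and staff who deliver or support the game, are not blinded.
2. Keep the stored sequence and external allocator, described as allocation concealment only. Delete the part of the closing clause that claims validity of the results.
3. Add to the limitations in the Discussion that outcomes are self-reported by respondents who know their arm.
4. Qualify the attribution statement in Data analysis: an effect of condition on a questionnaire may include the effect of knowing the allocation.
5. Where feasible, run the primary model on coded arm labels. The per-protocol set would have to be fixed first by someone else, because establishing who completed the game reveals the arm.
6. As a secondary clarification, say how execution by the external researcher and oversight by the principal investigator and team fit together, and who can see the sequence. Recruitment began in September 2024, so describe only what was actually done.

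The cost is a text edit and, for item 5, coded labels. Design, sample size and recruitment are unaffected. The downside is a less favourable risk-of-bias statement.
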